## Methods

### Study design

The *mindmom* study is a bicentric prospective randomized controlled trial (RCT) with a repeated measures and crossed-lagged panel design. Participants will be equally allocated to one of the two study arms: “8-week eMBI course” (intervention group) or “Treatment as usual (TAU) alone” (control group). Both groups will be compared regarding superiority of an electronic mindfulness-based intervention over TAU. The study is being conducted at the University women’s hospitals of Heidelberg and Tübingen, Germany. Ethics approval has been obtained from both universities.

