**Confirmative hypotheses**				
**1–3**	2 (group) × 7 (measurement)—ANOVA for repeated measures on the factor “measurement”	2	*F*-distribution	Group × measurement interaction effect
**4–6**	2 (group) × 5 (measurement)—ANOVA for repeated measures on the factor “measurement”	1	*F*-distribution	Group × measurement interaction effect

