**Exploratory hypotheses**				
**1–9 and 14–16**	2 (group) × 3 (measurement)—ANOVA for repeated measures on the factor “measurement”	4	*F*-distribution	Group × measurement interaction effect
**10–12**	2 (group) × 2 (measurement)—ANOVA for repeated measures on the factor “measurement”	1	*F*-distribution	Group × measurement interaction effect
**13**	*t* test for independent samples	1	*t*-distribution	Group main effect
**14**	One-dimensional *χ*^2^ test with 2 cells	3	*χ*^2^-distribution	Group main effect

The critical, local α-errors for the 3 tests evaluating the confirmatory hypotheses are Bonferroni-adjusted to α_local_ = .05/3 = .016 to avoid exceeding a global α-error of α_global_ = .05 by performing multiple tests. For the exploratory analyses, the critical, local α-errors are not adjusted and set to a conventional level of α_local_ = .05. Owing to inflation of the global α-error by multiple testing (9 tests) to α_global_ = 1 − (1 − 0.05)^9^ = 0.37, the exploratory analyses have a descriptive character and will be used to generate future hypotheses.

Dunn’s multiple comparison procedure is used as a post hoc test because it allows hypothesis-driven and economic multiple testing. This procedure results in a minimum significant difference (ψ). The test value is t-distributed. As effect sizes, partial η^2^ and ω^2^ are used. These are sample-based or population-based estimators of explained variances, respectively. According to Cohen [56], η^2^/ω^2^ = .01 represents small, η^2^/ω^2^ = .06 represents medium, and η^2^/ω^2^ = .14 represents large effects.

Furthermore, identified relationships are tested for causality. This can be done by means of the study’s cross-lagged panel design (outcomes and confounding variables are collected at multiple measurement times). Here, linear structural equation modeling is used.

In order to clarify the mediating mechanisms as well as the modifiability of the identified associations, additional explorative path analyses are performed on mediating and moderating processes according to Hayes’ regression-based approach [57] using the SPSS®—macro “PROCESS” (current v. 3.4).

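### The cross-lagged panel analysis is described as a test of causality, but on non-randomised variables it tests only lagged association

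*Protocol article*

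**What the plan says.** The Study design section of the protocol article describes a randomised trial with a "repeated measures and crossed-lagged panel design". In the Data analyses section, below Table 3, the article states that "identified relationships are tested for causality" and adds: "This can be done by means of the study’s cross-lagged panel design". The reason given is that "outcomes and confounding variables are collected at multiple measurement times". On method it says only: "Here, linear structural equation modeling is used".

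The same section says that "the exploratory analyses have a descriptive character and will be used to generate future hypotheses". That sentence follows the count of nine exploratory tests in Table 3, and the SEM is not in that table. The two analyses described next, the mediation and moderation path analyses and the multi-level models, are each marked as exploratory. The cross-lagged SEM carries no such mark.

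**The concern.** Randomisation protects one comparison, that between the arms. How one measured variable relates to a later value of another is observational, even inside a randomised trial. Measuring known confounders repeatedly does not deal with unmeasured ones, and the article names no assumptions under which a lagged path could be read causally.

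The article's own instruments suggest two further problems. Mindfulness is assessed as a personal trait and the STAI has a trait subscale, so part of the variation is probably stable between women. The EPDS has a reported internal consistency of 0.81, so its scores carry error. A cross-lagged model that allows for neither can give significant paths where no cross-effect exists.

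At stake are the trial's statements about mechanism, for example that mindfulness lowers later anxiety. As the text stands, a significant path could be published as causal evidence from a randomised trial.

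**Working it through.** **Which relations are protected.** The Randomization section allocates the arm 1:1. A path from allocation to a later outcome has the support of randomisation. A path from one outcome to another does not, whatever form of SEM is used. This step needs no arithmetic.

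**Inputs for the size of the problem.**
- From the article: N = 196 evaluable women (Sample size; 196/(1 − 0.30) = 280 recruited, as stated) and five pregnancy visits (Table 2).
- Conventional 5% two-sided level, as the article sets for its exploratory tests.
- Assumed, because the article gives no values: trait share w, trait correlation r_T, within-woman (state) correlation r_S, carry-over a from one visit to the next, reliability k.
- The article states no figure for the cross-lagged models, so there is none to reproduce.

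**Formula.** Take two standardised variables with no true cross-effect. Then:
- same-visit correlation: r0 = k[w·r_T + (1 − w)·r_S]
- own lag correlation: p = k[w + (1 − w)·a]
- cross-lag correlation: c = k[w·r_T + (1 − w)·a·r_S]
- expected cross-lagged coefficient, adjusting for the earlier value: b = (c − r0·p)/(1 − r0²)
- R² = (p² + c² − 2·p·c·r0)/(1 − r0²)
- SE = √[(1 − R²)/(193·(1 − r0²))], with 193 = 196 − 3
- rejection rate ≈ Φ(b/SE − 1.96) + Φ(−b/SE − 1.96)

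If k = 1 and r_T = r_S = r, then r0 = r and c = r·p, so b = 0. If w = 0 and k = 1, then r0 = r_S, p = a and c = a·r_S, so again b = 0. In these cases the test keeps its 5% level.

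**Results for one path between adjacent visits.**

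| w | r_T | r_S | a | k | b | SE | Rate, formula | Rate, simulation |
|---|---|---|---|---|---|---|---|---|
| 0 | – | .3 | .5 | 1 | 0 | .065 | 5% | 5–6% |
| .5 | .3 | .3 | .3 | 1 | 0 | .057 | 5% | 5% |
| 0 | – | .5 | .5 | .8 | .048 | .072 | 10% | 10% |
| .5 | .5 | .3 | .3 | 1 | .042 | .060 | 11% | 11–12% |
| .5 | .7 | .3 | .3 | 1 | .093 | .063 | 32% | 32% |
| .7 | .5 | 0 | 0 | 1 | .120 | .054 | 60% | 59% |

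Worked example, last row: r0 = .7 × .5 = .35, p = .7, c = .35. So b = (.35 − .245)/(1 − .1225) = .105/.8775 = .120. R² = (.49 + .1225 − .1715)/.8775 = .503. SE = √[.497/(193 × .8775)] = .054. The ratio is 2.21, and Φ(2.21 − 1.96) ≈ .60.

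The simulations fitted lagged regressions of each variable on both earlier values, with 1,000 or more runs per setting. With seven visits the two half-trait settings gave 11% and 33% per path, hence the quoted range of about 12–33%.

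**Holding a path equal across visits** pools the bias. With five and seven visits the rates were 28% and 41% (w = .5, r_T = .5, r_S = .3), 86% and 96% (r_T = .7), and 27% and 35% (no trait, reliability .8). They stayed at about 4–6% in the settings where b = 0.

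**Several paths.** Four independent valid tests already give 1 − 0.95⁴ = 18.5% with at least one significant result, so any figure for at least one of four paths must be read against that baseline.

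**The case against.** The strongest reply is that the article does not fix a standard cross-lagged model. Linear SEM also covers random-intercept and latent-variable versions, and the full protocol or an analysis plan may specify one. This stands: the error rates above apply only if stable differences or measurement error are left unmodelled. It does not rescue the wording. A random intercept removes stable confounding only. Unmeasured confounding that changes over time remains, so the analysis would still not be a test of causality.

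A second reply is that the false-positive rates depend on the inputs. This also stands. A reader might infer that cross-lagged models generally return spurious paths. The documents do not support that: the rate is nominal when trait and state correlations match, and the 59% needs states that are uncorrelated within a woman and do not carry over between visits. The article's own Background reports roughly 50% comorbidity of anxiety and depression, which makes wholly unrelated states hard to assume for that pair. The five-visit settings also do not describe mindfulness or cortisol, which Table 2 schedules only at T1, T5 and T7.

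A third reply is that the analysis is supplementary. It is not among the confirmatory tests, but the descriptive caveat does not expressly reach it. A reader might go further and infer that the trial's main conclusion would be wrong. It would not follow: that conclusion rests on the group-by-measurement interactions between randomised arms, which do not use this model.

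**Conclusion.** The statement that the cross-lagged panel tests causality is wrong as written, under any specification of the SEM, because the relations concerned are not randomised. This part rests on no numerical assumption.

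The size of the risk is conditional. If trait variance or measurement error is ignored, the single-path error rate at a nominal 5% lies between about 5% and about 59% over the settings examined, with about 12–33% when half the variance is stable, trait correlation is .5–.7 and state correlation is .3. None of these inputs can be checked from the article, so the range shows what can happen and does not predict this trial's error rate.

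Sample size, the confirmatory significance level and the confirmatory tests are untouched. The point is minor for the trial's main result, but it bears on what may be claimed about mechanisms.

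**What to change.** Replace the causal phrase with wording such as: examined for longitudinal (lagged) associations. Label the cross-lagged SEM exploratory, as its neighbouring analyses are, and reserve causal language for the comparison of the randomised arms. This costs a sentence or two.

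Optionally, add a sensitivity analysis that separates stable between-woman differences from within-woman change, where a variable has enough visits: EPDS and STAI have seven, PRAQ-R has five. It needs one latent intercept per variable and gives less precise lagged estimates. Mindfulness and cortisol have only three visits, so little can be expected from such a model there. It would not restore the causal wording in any case.

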### Sample size

Estimation of sample size and power analysis were calculated with G*Power (Version 3.1.9.2) [32, 33]. The estimation was implemented for the confirmatory hypotheses, which aim for interaction between the between- (group) and within-subject factor (time of measurement), i.e., that the symptom burden develops differently in the two study groups over the course of time. The analysis with the lowest power is the two-factorial ANOVA with the outcome “PRAQ” (5 measurements, see Table 3, hypotheses 4–6).

The estimation is based on type 1 error of α = .016, Bonferroni-adjusted for 3 confirmatory analyses, and a power of 1 − β = .90. The statistically significant effect size is based on the results of a pilot study on mindfulness-based prevention in pregnant women with a history of depression [34]. Based on the mean values, standard deviations, and case numbers reported in this study, a final treatment effect of Cohen’s *d* = .34 (intervention group: *M* = 4.90, *SD* = 5.22, *n* = 21; control group: *M* = 6.62, *SD* = 4.94, *n* = 29) is calculated for the outcome “depressive symptoms” (EDPS score). According to Cohen (1988), this can be classified as a small effect size. Thus, the number of cases for the ANOVA design is estimated for small treatment effects (*f* = .10). Thus, *N* = 196 cases are needed to evaluate the eMBI. Assuming a dropout rate of 30%, the number of cases was determined to be *N* = 280 to reach a case number of *N* = 196 (*n* = 140 for each group or per region and *n* = 70 per group and region). With a sample size of *N* = 196, large- (*f* = .40) and medium-sized (*f* = .25) effects can be detected with a power of 1 − β = .99 and .98, respectively. Only small effects (*f* = .10) cannot be ruled out sufficiently with a power of 1 − β = .27 in case of non-significant between-subject effects.

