Moreover, data will be analyzed by multi-level modeling. Hereby, the repeated measures (level 1) will be nested in the patients (level 2). A simulation study shows that only small samples on level 2 (< *n* = 50) lead to biased estimations of the standard errors on level 2 [58]. Expecting invariant results, the exploratory application of these models can increase the assurance regarding the exclusion of small between subject effects.

In accordance with the ICH Guideline E9, the primary analyses are performed according to the intention-to-treat (ITT) principle. Per-protocol (PP) analyses on sensitivity of effects are implemented in an exploratory fashion.

In order to reliably estimate missing values and thus to protect the analyses against response and selection biases, multiple imputations will be used [59]. First of all, missing values will be tested by Little’s Missing-Completely-At-Random test [60]. Following a negative result, *n* = 20 data sets with all variables of the analytic model are estimated. Hereby, value estimations are restricted to scale-specific ranges. Results are then pooled over the *n* = 20 data sets.

In accordance with the methods proposed by the German Institute for Quality and Efficiency in Health Care (IQWiG), the cost-effectiveness analysis will be carried out from the perspective of the statutory health insurance and, if possible, additionally include a societal and/or individual perspective [61]. The incremental cost-effectiveness ratio (ICER) will be calculated dividing the difference in costs by the difference in health benefit of the intervention compared to standard care. Costs are assessed in monetary units, and the benefit is measured by the primary (severity of symptoms) and secondary outcomes (f. e. cesarean sections, health related quality of life). The perspective of the analysis thereby determines the relevant cost components.

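### Agreement between multi-level models and the ANOVA cannot give assurance that small between-subject effects are excluded, because both analyse the same women and the same scores

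*Protocol article*

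**What the plan says.** Two places in the protocol article deal with the same gap.

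- **Sample size.** After deriving N = 196, the plan gives the power of the between-subject test. It is high for large and medium effects, but then: "Only small effects (*f* = .10) cannot be ruled out sufficiently with a power of 1 − β = .27 in case of non-significant between-subject effects".
- **Data analyses, paragraph on multi-level modeling.** The repeated measures are nested in the patients. A simulation study is cited to the effect that level-2 standard errors are biased only when there are fewer than 50 level-2 units. The paragraph concludes: "Expecting invariant results, the exploratory application of these models can increase the assurance regarding the exclusion of small between subject effects".

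The confirmatory tests are different ones. Table 3 names the group × measurement interaction as the relevant effect of all three. They are tested at α = .016, and the planned power refers to that interaction. Exploratory analyses are tested at an unadjusted α = .05 and are described as descriptive and hypothesis-generating.

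**The concern.** The Sample size section reads a non-significant between-subject test as ruling out an effect when power is high enough, and admits that this fails for small effects. The multi-level paragraph then offers agreement between two analyses as something that narrows the gap.

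Agreement would count as evidence only if it were less likely when a small effect exists than when none does. Two analyses of the same scores from the same women will nearly always agree, so seeing them agree says almost nothing about whether a small effect is present. The cited simulation does not help: a well-estimated standard error does not make the trial more able to detect or exclude a small difference. The sentence gives no confidence-interval criterion that could carry an exclusion claim.

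What is at stake is how a null group comparison is interpreted. The sentence invites more confidence in the absence of a small average benefit or harm than the data can supply.

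**Working it through.** **Inputs from the protocol article.** N = 196 evaluable (98 per arm under 1:1 allocation), 280 randomised (196 / (1 − .30) = 280), m = 5 measurements (PRAQ), f = .10 for a small effect, α = .016 per confirmatory test, α = .05 for exploratory tests.

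**Assumption.** The correlation ρ between repeated scores is not stated. I take ρ = .5, which reproduces the plan's figures, and show .3 to .7.

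**1. Reproduce the plan's figures.** For the between-subject test, λ = f²·N·m / (1 + (m − 1)ρ), noncentral F with 1 and N − 2 df.

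- f = .10: λ = .01 × 196 × 5 / 3 = 3.27, power .269 (plan: .27).
- f = .25: λ = .0625 × 196 × 5 / 3 = 20.4, power .981 (plan: .98).

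For the interaction, λ = f²·N·m / (1 − ρ) = .01 × 196 × 5 / .5 = 19.6, with 4 and 776 df. Power is .904 (plan: .90). Thus .27 and .90 belong to two different tests that share the label f = .10.

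**2. How often a true f = .10 between-subject effect is non-significant (1 − power, m = 5).**

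| N | α | ρ = .5 | ρ = .3 to .7 |
|---|---|---|---|
| 196 | .016 | 73% | 62% to 79% |
| 196 | .05 | 56% | 44% to 64% |
| 280, all complete | .016 | 60% | 46% to 69% |
| 280, all complete | .05 | 42% | 29% to 52% |

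The α = .05 rows are the relevant ones for the exploratory multi-level models. The N = 280 rows are an upper bound on information, because 30% dropout is expected.

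**3. Does agreement add anything?** In 600 simulated trials (N = 196, m = 5, ρ = .5, complete data, true f = .10, that is a constant group difference of .20 SD), the ANOVA between-subject test and a random-intercept model were fitted to the same data and judged at α = .016.

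- The two p-values correlated at .99999; the largest difference was .0016.
- When the ANOVA was non-significant, the multi-level model was too in 98.6% of runs.
- Both were non-significant in 70.7% of runs, although the effect was real in every run.

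Invariant results therefore arise almost always with a real small effect present.

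**4. What an interval would show.** The standard error of the mean group difference is (2/√N)·√((1 + (m − 1)ρ)/m) = (2/14)·√.6 = .111 SD. The 95% half-width is about .218 SD at N = 196 and ρ = .5, against .20 SD for f = .10. It is about .187 SD at ρ = .3, and about .182 SD with 280 complete records at ρ = .5. Whether a small effect can be excluded thus depends on the interval actually obtained.

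**The case against.** Several objections have force.

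- **The primary analysis is not touched.** The trial is sized for the interaction. A reader might infer that the trial has only .27 power for the effect it was designed to find; the documents do not support that, since the interaction has about .90 power. This stands in full.
- **The wording is soft.** The models are called exploratory, the sentence says only that they can add assurance, exploratory results are declared descriptive, and effect sizes (partial η², ω²) are planned. A reader might infer that the plan lets the evaluators report small effects as absent. No such rule is written, and the Sample size section openly says that small effects cannot be ruled out. This limits the consequence but does not make the inference valid.
- **73% uses the confirmatory α.** At the exploratory α = .05 the figure is about 56% at N = 196. With 280 complete records it is about 42%, and 29% at ρ = .3. This stands, and both levels are shown. Even 29% is too high for non-significance to exclude an effect.
- **Multi-level models may use partial records, and the simulation covers only complete data with a random intercept.** The article fixes neither random effects nor covariates, so agreement could be less close in practice. That is a reason to use the models as a check on missing-data handling. It does not turn agreement into evidence against a small effect.
- **Equivalence margins do not belong in a superiority trial.** Agreed: fixed margins are not needed to repair this sentence. Nor can one say that an observed difference of zero could never exclude .20 SD, because the half-width falls below .20 SD under some of the assumptions above.

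**Conclusion.** The point holds as a minor one. The stated inference, from invariant multi-level results to greater assurance that small between-subject effects are excluded, is not valid: the models reuse the same data, and the cited simulation answers a different question. Under ρ = .5 and 5 measurements, a true f = .10 between-subject effect is non-significant in about 73% of trials at α = .016 and 56% at α = .05 (N = 196), or about 60% and 42% with all 280 women complete. The correlation is an assumption, supported by its reproducing the plan's .27, .98 and .90.

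No confirmatory test, sample size or prespecified decision changes. The error concerns only how a null between-group result may be read.

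**What to change.** In the multi-level modeling paragraph of the Data analyses section:

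1. Delete the wording that agreement increases assurance about the exclusion of small between-subject effects.
2. Describe the multi-level models as a check of modelling and missing-data assumptions.
3. Add one sentence: any statement that a between-group effect of a given size is excluded will rest on the confidence interval for the group difference, not on non-significance or on agreement between models.

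The intervals come from models already planned, so no extra participants, data or analyses are needed. The cost is that a null result will support a weaker claim.

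### Multiple imputation in the confirmatory analyses depends on the result of Little's MCAR test, which leaves one branch without imputation and conflicts with the stated ITT principle

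*Protocol article*

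**What the plan says.** Three statements in the Data analyses section of the protocol article bear on this point.

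- On the analysis set: "the primary analyses are performed according to the intention-to-treat (ITT) principle".
- On missing values: multiple imputation is announced without condition, to guard against response and selection bias.
- On the procedure: Little's MCAR test is run first, and then "Following a negative result, *n* = 20 data sets with all variables of the analytic model are estimated". The article does not say whether 'negative' means that MCAR is rejected or that it is not rejected, and it gives no action for the other result.

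Table 3 makes the confirmatory tests repeated-measures ANOVAs, two over 7 measurements and one over 5, with the group × measurement interaction as the relevant effect. The software is SPSS. Multilevel models are also planned, but as an exploratory addition. The Sample size section counts on substantial loss ("Assuming a dropout rate of 30"%) and plans for 196 evaluable women out of 280.

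**The concern.** A pre-test decides whether the confirmatory analyses use imputed data. There are two readings.

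- If 'negative' means MCAR is not rejected, imputation is used when it is least needed and withheld when dropout is visibly selective.
- If 'negative' means MCAR is not supported, a non-significant test is taken as licence not to impute.

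On both readings one branch has no imputation. A repeated-measures ANOVA without imputation drops any woman with a missed visit, so that branch no longer analyses everyone randomised.

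The test also answers the wrong question. Multiple imputation is valid under MAR, and Little's test addresses only MCAR. At stake are the ITT status of the three confirmatory tests, their type I error if dropout differs by arm, and reproducibility, since two analysts could follow the same sentence in opposite directions.

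**Working it through.** **1. The plan's own figures.** Inputs from the Sample size section: "The estimation is based on type 1 error of α = .016, Bonferroni-adjusted for 3 confirmatory analyses"; "a power of 1 − β = .90"; "the number of cases for the ANOVA design is estimated for small treatment effects (*f* = .10"); and the 2 × 5 PRAQ design. The correlation between visits is not stated; ρ = 0.5 and ε = 1 are assumed. For the interaction, λ = f²·N·m/(1 − ρ), with df (m − 1) and (N − 2)(m − 1).

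- N = 196, m = 5: λ = 0.01 × 196 × 5 / 0.5 = 19.6, df 4 and 776, power 0.904. The smallest even N reaching 0.90 is 194, so the stated 196 is reproduced within tolerance.
- Dropout: 196 / (1 − 0.30) = 280, as stated.
- Sensitivity at N = 196: power 0.744 (ρ = .3), 0.826 (.4), 0.904 (.5), 0.964 (.6), 0.994 (.7).

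**2. Women lost on the branch without imputation.** 0.30 × 280 = 84 lost and 196 left. This is a planning figure and not a ceiling, because a single missed visit also removes a woman. Assuming 5% intermittent missingness per visit after T1:

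- 7 visits: 280 × 0.70 × 0.95⁶ ≈ 144 complete (51%), power 0.87.
- 5 visits: 280 × 0.70 × 0.95⁴ ≈ 160 complete (57%), power 0.81.

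At 10% the counts are about 104 and 129, each with power 0.69.

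**3. Does Little's test detect the dropout that matters?** Rejection rates at an assumed 5% level with about 30% dropout:

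| Dropout mechanism | 7 visits, N = 280, monotone dropout, 300 runs | 5 visits, 140 per arm, dropout before T5 driven by T4 |
|---|---|---|
| True MCAR | 4% | about 5% |
| Depends on score, same direction in both arms | 47% | 86% (log-odds +.1/+.1 per point) |
| Depends on score in one arm only | not run | 25% (+.1/0) |
| Depends on score, opposite directions by arm | 2% to 9% | 5% (+.1/−.1) |
| Not at random | 4% to 17% | not run |

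The test reacts most when both arms lose the same kind of woman, which does not bias the group contrast. It is close to silent when the arms lose different kinds.

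**4. Effect on the tested quantity.** Assumptions: 5 visits, SD 5, equal correlation .5, 30% dropout per arm before T5, logistic in the T4 score, and group difference growing linearly to −1.72 at T5. Complete-case results:

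- Slopes +.1/−.1: difference −0.72 at T1 and −2.44 at T5, so the change is −2.44 − (−0.72) = −1.72. At T4 it is −2.73 against a true −1.29.
- Slopes +.1/0: −0.35 at T1 and −2.08 at T5, so the change is −1.73.
- Equal slopes: no bias.

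Selection shifts T1 and T5 together, so the baseline-to-end contrast survives. The profile is distorted at T4, and the omnibus interaction test picks that up. With no treatment effect and a nominal level of .05/3 = 1.67%, the complete-case interaction test rejects in:

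- about 6.5% of runs with slopes +.1/−.1;
- about 3% with +.1/0;
- the nominal rate with equal slopes.

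If the correlation is instead AR(1) with .7 and slopes are opposite, the change itself is biased: −2.2 against −1.7.

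**The case against.** The strongest reply has four parts.

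- **The complete-case branch is nowhere written.** The article says imputation will be used, and the definition of 'negative' and the test level may sit in an analysis plan that is not shown. This stands in part: the branch is an inference. The conditional sequence, however, is in the text. With these ANOVAs, exploratory multilevel models and no other method named, no other outcome of the sequence is described.
- **The alarming reading of 'negative' is unlikely.** Given the stated purpose, it most naturally means that MCAR is not supported. That is fair. What then remains is reliance on a test with little power against arm-specific dropout.
- **The bias is easily overstated.** A reader might compare the raw T5 differences, −2.4 against −1.7, and infer that the treatment effect would come out about 40% too large. The documents do not support that. The confirmatory effect is the group × measurement interaction, the change from T1 is essentially unbiased under equal correlations, and the pattern needs opposite dropout slopes, for which the documents give no evidence. In the seven-visit scenarios the bias in change was at most about 0.03 SD. When dropout was spread over all visits, the interaction test stayed near nominal (1.4% to 2.8%).
- **Power is not lost.** A reader might infer that the trial becomes underpowered. At the planned 30% it does not: 196 complete cases keep about 90% power at ρ = .5.

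**Conclusion.** The point holds as an inconsistent rule with a poor trigger. The section promises ITT and imputation, then makes imputation conditional on a test that cannot show whether imputation is needed. By inference, one result leaves the three confirmatory tests as complete-case analyses, without about 84 of 280 randomised women at the planned dropout and more if single visits are missed.

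The statistical harm ranges from none (equal dropout slopes) to a type I error of about 6.5% against 1.67% (opposite slopes), with bias in change only under the AR(1) assumption. These figures rest on assumed SD, correlations and dropout models, because the documents give none. Severity: should fix.

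**What to change.** Delete the condition. State that multiple imputation is applied to all randomised women in the three confirmatory analyses whatever Little's test shows. Alternatively, make the likelihood-based multilevel model already planned the confirmatory analysis. Report Little's test as description only and the complete-case ANOVA as a sensitivity analysis.

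The cost is one sentence, with no new data and no change to N = 280. All 280 women stay in, 84 more than on the complete-case branch. With full information, power at f = .10 and ρ = .5 would be at most 0.984 (5 measurements) or 0.997 (7), against 0.904 and 0.966 with 196 complete cases; the real gain under imputation is smaller. Both options assume MAR and do not protect against dropout that depends on unobserved scores.
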